### Ethics approval and consent to participate

This study has Health Research Authority Confidentiality Advisory Group Section 251 approval to establish a legal and ethical basis for linking data. In addition, this study has Health Research Authority ethical approval via the West Midlands South Birmingham Research Ethics Committee, reference 18/WM/0140. The data will be kept anonymised after data-linkage. Qualitative substudy participants will provide written informed consent for participation. The consent process includes provision of participant information sheet with the opportunity to ask questions. Only adults aged 18years and over will be invited and included.

Regarding current progress at time of publication, the data linkage for this study is currently in progress and has not yet been completed. Recruitment for focus groups has been initiated on 25/05/2023 with predicted completion of recruitment 01/05/2026. Data collection and linkage is estimated to be completed 01/07/2025. The predicted study end date with final results for the study is 01/11/2026.

## Discussion

This will be the first virtual in-silico trial comparing targeted screening and population screening of AAA. The objective of the study is to assess the clinical and cost-effectiveness of targeted AAA screening, aiming to establish its viability as a solution to the declining cost-effectiveness of population-based AAA screening programs. Patient and public engagement has been central to the study from its inception and will remain integral throughout its implementation. Focus groups consisting of beneficiaries of screening and members of the public will help frame the success criteria and acceptability thresholds of the quantitative outputs, enhancing the relevance and applicability of the study’s findings.

This project’s strengths are founded on its mixed-method approach, utilization of a substantial real-world dataset (the largest linkage of national screening data to date), application of an established statistical model (DES model) combined with strong patient and public involvement. Multiple work packages provide a multimodal overview to address the research question.

Only an estimated 20% of the entire dataset will be available for linkage with primary care data, which itself has numerous inherent limitations (data incompleteness, coding variability, and selection bias). Despite this, the large sample size will have adequate sensitivity and power to develop, validate and test proposed risk stratification models. Multiple strategies may have to be employed to account for potential missing data. While multiple imputation remains one of the more widely used approaches, its appropriateness in prediction settings is debated. Multiple imputation generally assumes data is missing at random which is unlikely to be true in primary care records. Therefore, multiple imputation may introduce bias and limit generalisability. Sensitivity analyses will be essential to evaluate model performance across key subgroups and it will be important to explore if missingness itself carries a predictive value.

It is also possible that the predictive models generated in work package 1 do not maintain sufficient disease detection rates and that the best predictors for these models are obtained from primary care data recorded after the AAA screening appointments. Further subset (including temporal) and sensitivity analysis will be performed to account for this. The DES model, published in 2018, requires updating and contains multiple inherent assumptions. This will be updated in the study with up-to-date parameters reflecting the current modern natural history of AAA, screening compliance and costs.

Strategies for targeted AAA screening have previously been investigated in Australian and Danish screening study datasets [33,34]. Whilst these studies both concluded that disease detection rates for targeted screening were too low to be acceptable, these studies were based on a different age range of men than that invited in NAAASP, were performed at a time when disease prevalence was higher, and did not examine the use of primary care data as a method for cohort identification. Furthermore, no cost-effectiveness analyses were performed in either study and no other economic assessment of targeted AAA screening has been performed. No randomized controlled trials have been performed for targeted screening. Further research is needed to assess the feasibility, effectiveness, and cost-effectiveness of targeted AAA screening. This study aims to address these gaps.

We expect this project to have a direct and meaningful impact on NHS, UK and worldwide AAA screening policies. Our dissemination strategy will be to target those involved in screening policy decisions and the public via conventional media. The study findings will be submitted for publication in peer reviewed journals and presented at scientific meetings.

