**Fig 1 pone.0327856.g001:**
[figure not shown]
Data flow diagram for data linkage between NAAASP and CPRD. NHSE – NHS England, NECSWS – NEC software solutions, SCWDSCRO – South Central & West Data Services for Commissioners Regional Office, CPRD – Clinical Practice Research Datalink, EMIS/Vision – GP software from where data derives, CAG – health research authority confidentiality advisory group.

Data from the NAAASP will cover an eleven-year period from 2013 to 2024, thus we expect to have screening records for over 2,500,000 men invited for screening and over 25,000 men with AAAs. Primary care data will be obtained from the Clinical Practice Research Datalink (CPRD). CPRD is a database of anonymised primary care medical records covering over ~19 million patients from 1927 different UK GP practices [16–19]. Coding of clinical events in CPRD has been both technically and clinically validated [20–26]. We estimate that at least 20% of men invited for screening between 2013 and 2024 will be currently registered with GP practices contributing to CPRD.

We will undertake data linkage using the CPRD’s established pathway and patient level data-flow model for non-standard linkages. For this study both CPRD Aurum and CPRD GOLD datasets will be extracted.

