### Work package 2 (WP2)

The aim of WP2 is to determine what the main risk factors for screen-detected AAA are, using the linked dataset generated in WP1 and thus develop hypothetical targeted screening strategies.

Known and putative AAA risk factors (smoking, hypertension, hyperlipidaemia, diabetes (protective factor)) will be tested for association with screen-detected AAA to determine their potential for use as sole criteria for targeted screening. Multivariable risk prediction modelling will be used to identify a set of clinical variables that can be used as criteria for targeted screening. Predictors for inclusion in the model will be selected based on mathematical/statistical performance and no predictors will be forced into the model based on prior assumptions.

If the final model is based on a small number of variables, adaptation for clinical and public use will also be considered. The target population for the model will be the same as the population in which it is developed, ensuring the relevance of the model to future clinical practice.

The primary performance criterion for the model will be achieving a predefined sensitivity threshold for detecting true positive cases in targeted AAA screening. This success criterion and/or the success threshold may be revised depending on the outputs from ethical study and focus groups. Sensitivity analyses to test variable selection strategies will be performed and the TRIPOD checklist will be used to present overall model results [27].

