### Work package 3 (WP3)

Work package 3 consists of the following three tasks: Reviewing and updating an established discrete event simulation model (DES) of AAA screening, conducting in-silico trials of targeted vs population screening for AAA to determine the diagnostic accuracy of targeted screening and modelling the long-term effectiveness of targeted vs population screening using DES modelling.

In the ‘Screening Women for aortic ANeurysm’ (SWAN) project [10], a new DES model of AAA screening was developed to estimate the clinical and economic effectiveness of screening over a 30-year period [28]. The model provides outputs in terms of the number of clinical events, life-years gained with screening and incremental cost-effectiveness ratios (cost per quality-adjusted life-year gained) for a follow-up period of 30 years after screening. The model allows individual screening parameters to be varied and has been used to estimate the clinical and economic effects of varying surveillance intervals for men with small AAA in the NAAASP [28]. In this study, we will adopt the DES model to estimate the effectiveness and cost effectiveness of targeted AAA screening compared with whole population screening. We will populate the model using the data from in-silico trials.

The linked NAAASP-primary care dataset will be used to test the targeted AAA screening strategies developed in work package 2. This will conform to the following clinical trial structure:

(P)opulation: Men in the year of their 65th birthday (current AAA screening population)

(I)ntervention: Risk-factor targeted invitation for AAA screening

(C)omparison: Whole population screening

(O)utcome: Diagnostic effectiveness of targeted screening

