In-silico trials will then be run using the full range of targeted screening strategies determined in work package 2. Significant risk factors (such as smoking) will be examined as criteria for screening, both in isolation and in combination. The primary outcome for these in-silico trials will be diagnostic effectiveness (sensitivity and specificity, positive and negative predicative values, likelihood ratio, diagnostic odds ratio and area under the receiver-operator characteristic curve). Secondary outcomes will be those required to re-parameterise the DES model (re-invitations, attendance, non-visualisation, AAA size distribution at screening, AAA prevalence at screening and proportion of AAAs detected). For each screening strategy, individuals will be categorized into invited and non-invited groups. In each of these groups, the actual screening outcomes will be known and using the true detection rate the overall proportional detection rate for each hypothesized screening strategy can be calculated.

The trial outputs from each targeted screening scenario examined will be compared for their effect on long-term clinical and cost-effectiveness. Absolute numbers of clinical events for the varying screening scenarios can be calculated using the DES model and used to compare clinical outcomes using the reference case scenario of whole-population invitation for screening as a comparator. Clinical results will be presented as changes to the number of clinical events, principally proportional AAA detection and AAA mortality but including the effect of quality-adjusted life years. Outcomes will be presented as the incremental cost per quality adjusted life gained and incremental net monetary benefit (INMB) between targeted screening and whole population screening. Sensitivity analyses will be conducted to explore the key assumptions used in the model; the effect of varying the methods for calculating smoking status, hypertension and hyperlipidaemia will be examined as well as additional sensitivity analyses for coding variations in any strong predictors of AAA identified in the risk prediction modelling exercise. Additional analyses relating to the management and delivery of both AAA screening and vascular surgical services will be considered on a case-by-case basis.

### Medical ethics work package 4

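### The article does not exclude predictors recorded after the screening scan from the primary model, so the main accuracy results and the simulation inputs are open to leakage from the diagnosis

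*Protocol article*

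**What the plan says.** All references are to the protocol article.

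- **Work package 3 (WP3)** gives the intervention as "Risk-factor targeted invitation for AAA screening" and the population as men in the year they turn 65. "The primary outcome for these in-silico trials will be diagnostic effectiveness", which includes sensitivity, specificity and AUC. The trial outputs then populate the discrete event simulation (DES).
- **Work package 2 (WP2)**: "Predictors for inclusion in the model will be selected based on mathematical/statistical performance", and none is forced in on prior assumptions. "The primary performance criterion for the model will be achieving a predefined sensitivity threshold for detecting true positive cases in targeted AAA screening".
- **Discussion**: the limitations paragraph allows that "the best predictors for these models are obtained from primary care data recorded after the AAA screening appointments". The response is: "Further subset (including temporal) and sensitivity analysis will be performed to account for this".
- **Work package 1 (WP1)**: "Data from the NAAASP will cover an eleven-year period from 2013 to 2024". Men screened early can therefore have up to about 11 years of GP records after the scan.

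The article gives no index date for predictors in the primary model or the main in-silico trials.

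**The concern.** An invitation precedes the scan. A code entered because the scan found an aneurysm did not exist when the invitation decision would have been made. If such a code enters the model or a targeting criterion, part of the outcome is being used to predict itself.

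Three features of the plan make this more than a theoretical worry:

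- Selection on statistical performance favours variables that the diagnosis itself affects.
- The 4:1 training:testing split (Sample size calculation) would not expose the problem, because both parts would carry the same leak.
- The sensitivity analyses named in WP3 vary how smoking, hypertension and hyperlipidaemia are derived or coded. They do not vary when the information was recorded.

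At stake are the primary diagnostic accuracy results. Through the DES, so are AAA detection, AAA mortality, cost per QALY and net monetary benefit, which could describe a strategy that cannot be run at the time of invitation.

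**Working it through.** **1. The plan's own precision figures.** Sample size calculation: 5,000 AAA cases, α = 0.05 (taken as two-sided, z = 1.96), margin ±1.5 points at 70% sensitivity and ±1.25 points at 75%. The number of cases needed is n = z²·p(1−p)/d².

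- 70%, d = 0.015: 3.8415 × 0.21 / 0.000225 → 3,586
- 75%, d = 0.0125: 3.8415 × 0.1875 / 0.00015625 → 4,610

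Both are below 5,000, so the plan's statement is reproduced. With 5,000 cases the half-width, z·√(p(1−p)/n), is 1.27 points at 70% and 1.20 points at 75%.

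**2. Bias for a single-factor criterion.** Let S be sensitivity using pre-scan records only. Let f be the share of AAA men missed by those records who gain the code after the scan because of the diagnosis.

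Apparent sensitivity = S + (1 − S)·f, so bias = (1 − S)·f.

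The documents do not give f; it is an assumption. The values of S are the article's expected range for smoking alone (45% to 85%) and its two precision points.

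| S | f = 5% | f = 10% | f = 20% |
|---|---|---|---|
| 45% | 47.75% | 50.5% | 56% |
| 70% | 71.5% | 73% | 76% |
| 75% | 76.25% | 77.5% | 80% |
| 85% | 85.75% | 86.5% | 88% |

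**3. The value of f at which bias equals the stated margin.** f = margin / (1 − S).

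- 70%: 0.015 / 0.30 = 5%
- 75%: 0.0125 / 0.25 = 5%

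A larger sample narrows the interval but leaves this bias unchanged.

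**4. A model set to a sensitivity threshold.** If the cut-off is chosen to meet a predefined sensitivity, apparent sensitivity is fixed by design and step 2 does not apply. A leaked predictor raises the scores of AAA men, so a stricter cut-off still reaches the threshold and fewer men without AAA lie above it. The error then shows as overstated specificity and too small a proportion invited. The documents give nothing from which to size this.

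**The case against.** The strongest reply is that the Discussion sentence is a limitation worded as a possibility and sets no rule. A temporal subset analysis may well be one restricted to pre-scan records, which is close to the remedy proposed here. The WP3 intervention, WP2's stated aim of relevance to future practice and the commitment to TRIPOD reporting all suggest that unusable predictors are not intended. Index dates and look-back windows are also details that an article commonly leaves to the full protocol or SAP.

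Much of this stands. A reader might infer that the plan deliberately admits post-scan predictors to the main model, or selects on performance and nothing else. The text says neither. WP2 describes how to choose among candidates and does not define the candidate set.

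Nor is every later code spurious. Ever-smoking first recorded after the scan may be a true earlier exposure recorded late, and an update made in all men alike need not inflate sensitivity. That a detected AAA prompts new codes is plausible, but the documents do not state it.

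What the reply does not remove is that the article raises the timing problem itself and assigns it to further subset and sensitivity analyses. If the temporal subset is the pre-scan restriction, the estimate that could be put into practice is a secondary one, and the order should be reversed.

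**Conclusion.** The concern holds in a limited form, with moderate confidence, and should be fixed. The article foresees post-scan predictors, does not exclude them from the primary model, and states only secondary analyses as the answer. For an invitation strategy, this leaves the primary accuracy results and the DES inputs open to bias: in apparent sensitivity for single-factor criteria, and in specificity and the proportion invited for a model tuned to a threshold.

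The size cannot be derived from the documents. With an assumed f of 5%, the bias is 1.5 points at 70% sensitivity and 1.25 points at 75%, the same as the stated margins. Larger assumed values of f give larger biases, and a reader might take those as an estimate of the inflation. They are not one: f is unknown, and the formula applies only to single-factor criteria and only to coding caused by the diagnosis.

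**What to change.** State in WP2 and WP3 that the primary model, every targeting criterion and the in-silico trials that feed the DES use only primary care records dated before the man's NAAASP invitation, with the same rule for attenders and non-attenders. Keep analyses that use later-dated records as labelled secondary checks, for example for late recording of long-standing exposures such as ever-smoking, and do not pass their results to the DES.

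The cost is a few sentences and a date filter on the extract. The article reports that linkage was not complete at publication, so the rule could be set before the linked data are analysed. The price is that apparent performance may fall and some men will have no usable pre-invitation record, of smoking in particular.
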